## Abstract

**Background:**

Metabolic surgery induces rapid remission of type 2 diabetes mellitus (T2DM). There is a paucity of high level evidence comparing the efficacy of the laparoscopic Roux-en-Y gastric bypass (RYGB) and the laparoscopic one-anastomosis gastric bypass (OAGB) in glycemic control. Also, the mechanisms that drive the conversion of T2DM in severe obese subjects to euglycemia are poorly understood.

**Methods:**

The DIABAR-trial is an open, multi-center, randomized controlled clinical trial with 10 years follow-up which will be performed in 220 severely obese patients, diagnosed with T2DM and treated with glucose-lowering agents. Patients will be randomized in a 1:1 ratio to undergo RYGB or OAGB. The primary outcome is glycemic control at 12 months follow-up. Secondary outcome measures are diverse and include weight loss, surgical complications, psychologic status and quality of life, dietary behavior, gastrointestinal symptoms, repetitive bloodwork to identify changes over time, glucose tolerance and insulin sensitivity as measured by mixed meal tests, remission of T2DM, presence of non-alcoholic fatty liver disease/non-alcoholic steatohepatitis in liver biopsy, oral and fecal microbiome, cardiovascular performance, composition of bile acids, and the tendency to develop gallstones.

**Discussion:**

The DIABAR-trial is one of the few randomized controlled trials primarily aimed to evaluate the glycemic response after the RYGB and OAGB in severe obese patients diagnosed with T2DM. Secondary aims of the trial are to contribute to a deeper understanding of the mechanisms that drive the remission of T2DM in severe obese patients by identification of microbial, immunological, and metabolic markers for metabolic response and to compare complications and side effects of RYGB and OAGB.

**Trial registration:**

ClinicalTrials.gov NCT03330756; date first registered: October 13, 2017.

**Supplementary Information:**

The online version contains supplementary material available at 10.1186/s13063-022-06762-3.

## Background

Metabolic surgery has proven to be a successful long-term solution in the treatment of severe obesity and its comorbidities. It induces rapid remission of type 2 diabetes mellitus (T2DM) and is more effective than intense medical treatment [1–6]. Although the incidence of (severe) obesity and T2DM are on the rise, it is undecided which metabolic procedure has the most optimal risk-to-benefit ratio in terms of the effect on T2DM, post-operative complications and side-effects [3]. Some favor the Roux-en-Y gastric bypass (RYGB) over the sleeve gastrectomy in patients with T2DM, but despite its good results, the RYGB is considered an advanced and complex procedure [7]. The one-anastomosis gastric bypass (OAGB) has been introduced in 2001 as a novel and simplified variant of the RYGB. Available single-arm studies report favorable results of OAGB in the treatment of T2DM and, although little evidence is available comparing the efficacy of RYGB and OAGB in the treatment of T2DM, some suggest a benefit from OAGB over RYGB [8–14]. To the best of our knowledge, the DIABAR-trial is one of the few randomized controlled trials with primary endpoint to evaluate the glycemic response after laparoscopic RYGB and OAGB in patients diagnosed with severe obesity and T2DM, with up to 10 years of follow-up. The DIABAR-trial will clarify the benefit of these two procedures in the treatment of T2DM and directly compare complications and side effects, which will aid patients and physicians in an evidence-based decision upon the most optimal metabolic procedure. The secondary aim is to phenotype the patients enrolled in the trial and to identify driving mechanisms in the interplay between obesity and metabolic disease by identification of microbial, immunological and metabolic markers for metabolic response.

## Methods/design

### Objective of the study

The primary objective of the study is to compare glycemic control 12 months after RYGB and OAGB. Secondary aims of the study are to evaluate remission of T2DM (up to 10 years follow-up), weight loss, surgical complications, psychologic status and quality of life, dietary behavior, gastrointestinal symptoms, to phenotype patients and to identify driving mechanisms in the interplay between obesity and metabolic disease. To this end, extensive data collection will be performed. This data collection includes the assessment of liver biopsies obtained during surgery upon the presence of non-alcoholic fatty liver disease (NAFLD)/non-alcoholic steatohepatitis (NASH), oral and fecal microbiome, cardiovascular performance, glucose tolerance and insulin sensitivity as measured by mixed meal tests (MMTs), repetitive bloodwork to identify changes over time, biopsies of adipose tissue and jejunum during surgery, the composition of bile acids, and the tendency to develop gallstones. This data will be used to identify microbial, immunological and metabolic markers for metabolic response.

### Study design and sites

The DIABAR-trial is a two-armed, multi-center, open randomized controlled clinical trial comparing the effect of the RYGB (control) and the OAGB (intervention) on glycemic control. Participating centers are the Spaarne Gashuis (Hoofddorp, the Netherlands), MC Slotervaart (Amsterdam, the Netherlands), and the Franciscus Gasthuis (Rotterdam, the Netherlands). The DIABAR-trial started in October 2017 at MC Slotervaart (Amsterdam, the Netherlands) and the trial continued in March 2019 at the Spaarne Gasthuis (Hoofddorp, the Netherlands) by the same surgical staff and research team. In August 2020, the Franciscus Gasthuis (Rotterdam, the Netherlands) was added as a participating center. Materials will be stored in the DIABAR-biobank, which is located in the affiliated Amsterdam University Medical Center (AUMC) (Amsterdam, the Netherlands). Study materials will be processed in the laboratory of the AUMC and in the Wallenberg laboratory (University of Gothenburg, Gothenburg, Sweden).

The DIABAR-trial is closely related to the BARIA-study, a longitudinal cohort study in 1500 patients with severe obesity. In the BARIA study, systems biology is used to identify microbial, immunological, and metabolic markers for metabolic response prior to and after bariatric surgery [15]. The BARIA-study is conducted at the Spaarne Gasthuis and the existing infrastructure of the BARIA-study can be used in the DIABAR-trial. This explains why patients participating from the Spaarne Gasthuis will be asked to partake in a more extensive study protocol than patients enrolling from the Franciscus Gasthuis (Table 1). In Fig. 1 an outline of study enrolment, randomization, intervention and follow-up is shown.

**Table 1 Tab1:** Study procedures in the Spaarne Gasthuis and the Franciscus Gasthuis

		Enrolment allocation	Post-allocation								
Timepoint		***t***=-2	***t*** = -1	***t*** = 0	***t*** = 1	***t*** = 2	***t*** = 3	***t*** = 4	***t*** = 5	***t***=6-9	***t***=10
	Medical center	Screening	< 42 days of surgery	Day of surgery	14 D	42 D	6 M	1 Y	2 Y	3,4,5,10 Y	Re-operation^**a**^/endoscopy
**Enrolment/allocation**											
Eligibility screen	SG/FG	x									
Informed consent and allocation	SG/FG	x									
**Demographics**											
Medical history	SG/FG	Reg	x				x	x	x	x	
Medication check	SG/FG	Reg	x	x	x	x	x	x	x	x	x
**Biometrics**											
Physical examination	SG/FG	x	x	x		x	x	x	x	x	
CO/SVR/BS	SG		x					x	x		
**Blood**											
Laboratory work	SG/FG	Reg		Reg			Reg	Reg	Reg	Reg	Reg
MMT	SG		x					x	x		
Extra blood samples	SG		x	x				x	x	x	x
**Questionnaires**											
Psychological questionnaires	SG/FG		x				x	x	x	x	
GIQLI	SG/FG		x					x	x	x	
Dietary and satiety list	SG		x					x	x		
**Oral, fecal, and urine samples**											
Urine sample	SG				x	x	x			x	
Feces sample	SG				x	x	x			x	
24-h feces and urine	SG			x				x	x		
Oral microbiome	SG		x					x	x	x	
**Surgery and tissue samples**											
RYGB or OAGB	SG/FG			x							
Small intestine tissue sample	SG			x							x^a^
Subcutaneous adipose tissue	SG			x				x	x		x
Visceral adipose tissue	SG			x							x
Omental tissue	SG			x							x
Liver biopsy	SG			x						x	x
Portal blood sample	SG			x^a^							x^a^
Bile acids and bile salts	SG			x^a^							x^a^
Surgical endpoints	SG/FG				x	x	x	x	x	x	
**Other**											
Ultrasound gallbladder	SG		x^a^					x^a^	x^a^		

*BS* baroreflex sensitivity, *MMT* mixed meal test, *D* days, *CO* cardiac output, *GIQLI* gastro-intestinal quality of life, *FG* Franciscus Gasthuis, *FU* follow-up, *M* months, *OAGB* one-anastomosis gastric bypass, *SG* Spaarne Gasthuis, *SVR* systemic vascular resistance, *RYGB* Roux-en-Y gastric bypass, *Reg* regular, *t* time, *Y* year

^a^If applicable

**Fig. 1 Fig1:**
[figure not shown]
Outline of study enrolment, randomization, intervention and follow-up. *FG* Franciscus Gasthuis, *FU* follow-up, *MMT* mixed meal test, *M* month, *OAGB* one-anastomosis gastric bypass, *RYGB* Roux-en-Y gastric bypass, *SG* Spaarne Gasthuis,* t* time, *W* week

### Study population

The study population will consist of 220 severely obese subjects diagnosed with and treated for T2DM who are scheduled for bariatric surgery.

### Inclusion criteria

Male and female patients, aged between 18 and 65 years and with a BMI of at least 35 kg/m^2^ at intake and 50 kg/m^2^ or less on the day of surgery, are eligible for participation in the study. Only patients with proven T2DM, Hba1c > 7.0% at diagnosis, and treated with glucose-lowering agents at intake at the bariatric outpatient clinic or at least 2 months prior to surgery, and with an American Society of Anesthesiologist Classification (ASA) of three or less will be enrolled in the study.

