### Informed consent and randomization

Patients are first informed on the study during the preoperative screening program, which consists of consultations with a surgeon, an internist, a dietician, a psychologist, and meetings for patient education. If patients proceed towards surgery, they are screened for inclusion into the study. Patients are asked for written informed consent to participate in the study by the surgeon and also to store study materials in the DIABAR-biobank. After informed consent is obtained by the surgeon at the outpatient clinic, patients will be randomly assigned by the surgeon to undergo a RYGB or OAGB in a 1:1 ratio. Randomization will be performed with the use of electronic block-randomization with the program *Castor Electronic Data Capture* (Ciwit BV, the Netherlands). Block size varies between four and six; there is no stratification. Patients and surgeons are directly informed on the outcome of the randomization.

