### Treatment

All patients receive pre-, peri-, and post-operative care according to the local bariatric protocol. All patients are urged to lose bodyweight before surgery to decrease surgical risks. Patients are not required to undergo a low calorie liquid diet prior to surgery. Thrombosis prophylaxis is administered in the first post-operative week and a proton-pump inhibitor is prescribed for 3 months after surgery. Patients are advised to lifetime use of vitamins. Initial diabetes management after surgery is coordinated by the internist and during the first months after surgery transferred to a patient’s own diabetes team.

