#### Analysis of endpoints

The statistical analyses will be performed using SPSS statistical software (IBM corporation, New York, USA). Data will be expressed as mean, standard deviation, or median and range, as appropriate. Differences in categorical variables will be evaluated with the chi-square or the Fisher exact test, as appropriate; continuous data will be compared with the Student *t* test or Mann-Whitney *U*. Multivariate analysis and ANOVA for repeated measures will be used. *P*-values < 0.05 will be considered statistically significant. Clinical complications will be evaluated by an independent adjudication committee. An interim analysis will be performed at 60 patients per group. A modified intention to treat analysis will be performed (all randomized patients that initiate treatment in the arm they are allocated to, i.e., exempting those who do not undergo surgery at all) in which “last value carried forward” will be used for missing observations. A per-protocol analysis will be carried out as well to account for effects of revisional surgery (i.e., revision from OAGB to RYGB). For this analysis, only data of patients gathered before revisional surgery will be used.

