The underlying physiological and molecular mechanisms responsible for the antidiabetic effects of metabolic surgery have not been fully understood. Proposed theories include acute reduced caloric intake possibly-in part-responsible for the weight-independent antidiabetic effect occurring directly post-surgery, as well as a middle-to long-term antidiabetic effect of surgery-induced weight loss [50]. Rapidly occurring enhanced glycemic control might also be due to altered anatomy and signaling/sensing of the gastro-intestinal tract, formulated in the foregut and hindgut hypothesis [51, 52]. Among other factors that are recognized to be of potential influence are the immune system, the intestinal microbiome, and altered bile acid metabolism [53–56]. Also, there is an association between obesity, non-alcoholic fatty liver disease (NALFD), and insulin resistance/T2DM, with reports of the presence of (some form of) NAFLD in up to 80% of patients undergoing weight loss surgery [57, 58]. It is likely that not one (dominant) factor or one mechanism is responsible for the beneficial glucoregulatory effects of metabolic surgery but that the effects are due to an interplay of various pathways. The DIABAR-trial grants the unique opportunity to assess extensive data of patients with T2DM and obesity after two different metabolic procedures and to explore driving mechanisms in metabolic response.

A few limitations have to be acknowledged. First, for logistic reasons, patients will not be stratified upon the use of insulin or the duration of T2DM. Second, the authors are aware of and responsible for the extent of the study procedures patients are subjected to. Therefore, the study is performed by a research nurse, who stays in close contact with participating patients and monitors how patients perceive their participation in the study. To meet with the patient’s time investment, patients receive a financial reimbursement. Third, patients are required to lose weight prior to surgery. This might influence the metabolic changes induced by surgery; yet patients in both arms of the study are projected to the same pre-surgical weight loss and it lowers the surgical risk.

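### The upper BMI limit is judged on the day of surgery, after patients are randomised and told their arm, so eligibility is not settled at allocation

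*Protocol article*

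**What the plan says.** All references are to the protocol article.

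- **Inclusion criteria.** The two BMI limits carry different dates. The lower applies to patients "with a BMI of at least 35 kg/m^2^ at intake"; the upper reads "50 kg/m^2^ or less on the day of surgery, are eligible for participation in the study". No upper limit is given for intake or for randomisation.
- **Informed consent and randomization.** Allocation comes before the day of surgery: "After informed consent is obtained by the surgeon at the outpatient clinic, patients will be randomly assigned by the surgeon". The arm is disclosed immediately: "Patients and surgeons are directly informed on the outcome of the randomization".
- **Table 1.** The row "Informed consent and allocation" is marked in the screening column (t = -2). Surgery is t = 0. Physical examination is marked at both centres at screening, at t = -1 (within 42 days of surgery) and at t = 0.
- **Treatment and Discussion.** Treatment says "All patients are urged to lose bodyweight before surgery to decrease surgical risks". The limitations paragraph of the Discussion says "patients are required to lose weight prior to surgery".
- **Analysis of endpoints.** The main analysis is a modified intention-to-treat analysis of randomised patients who start treatment in their allocated arm, "exempting those who do not undergo surgery at all".

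**The concern.** An eligibility criterion should be decidable when the patient is allocated. This one depends on a measurement that does not yet exist. Anyone randomised above 50 in the hope of reaching the limit, or who gains weight after allocation, has an eligibility status that is settled only later, in an open trial where patient and surgeon both know the operation assigned.

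The analysis set makes this more than a formality. If such a patient is not operated on at all, the no-surgery exemption takes the patient out of the main analysis. The reason is then a post-randomisation value, pre-operative weight, which may plausibly be related to later glycaemic response. The groups compared would no longer be exactly the groups randomised, and a larger sample does not repair that.

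**Working it through.** **1. Order of events.** The point rests on sequence, so the sections are set side by side.

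| Step | Time in Table 1 | Arm known? | Upper BMI limit decidable? |
|---|---|---|---|
| Consent and allocation | t = -2 | Yes, from this moment | No |
| Pre-operative visit | t = -1 | Yes | No |
| Day of surgery | t = 0 | Yes | Yes |

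The criterion first becomes decidable two scheduled time points after allocation.

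**2. What can happen to a randomised patient above 50 at t = 0.**
- Operated on, then or later: formally ineligible, but kept by the modified intention-to-treat definition.
- Never operated on: removed by the no-surgery exemption.

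Only the second route changes the analysis set.

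**3. The plan's own figure.** The sample size section gives 100 per group, 10% dropout and 220 in total. 200 × 1.10 = 220; dividing instead, 200 / 0.90 = 222.2, rounded up to 223, is close. The 100 per group cannot be reproduced, because no 12-month difference or SD is given. Solving backwards (two-sided 5%, 80% power):

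d = √(2/100) × (1.960 + 0.842) = 0.396 SD.

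If the pre-operative SD of 1.4 to 1.5 applied at 12 months (assumption), this is 0.55 to 0.59 HbA1c points.

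**4. Effect on power, as illustration only.** The share of patients near BMI 50 is not given. Assume that a share x of those randomised is lost through the limit, on top of 10% dropout. Then n per arm = 110 × 0.90 × (1 − x), and power = Φ(0.396 × √(n/2) − 1.960).

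| x (assumed) | Patients of 220 | n per arm | Power |
|---|---|---|---|
| 0% | 0 | 99.0 | 79.6% |
| 2% | 4.4 | 97.0 | 78.8% |
| 5% | 11 | 94.1 | 77.5% |
| 10% | 22 | 89.1 | 75.3% |

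**5. Effect on the estimate, as illustration only.** If a share p of one arm is removed and the removed patients' mean HbA1c differs by D from that of the rest, the arm mean shifts by p × D. Take the extreme case of loss in one arm only, with D = 1.5 (one pre-operative SD, assumption):
- p = 5%: 0.05 × 1.5 = 0.075 points.
- p = 10% (11 of 110 patients): 0.10 × 1.5 = 0.15 points, about a quarter of the implied 0.59.

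If p = 0, or if the loss is equal in both arms with the same D, there is no shift.

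**The case against.** The strongest reply is that the exposure is narrow and its size unknown. Several stronger readings are tempting, and the article does not support them.

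- **A reader might infer that the urged weight loss is a run-in placed after randomisation.** The article says only that it precedes surgery. Patients go through a preoperative programme that includes a dietician before they are screened for the study, so some or most of the loss may come before allocation. The length of the gap is not given.
- **A reader might infer that weight loss makes patients ineligible.** It moves them towards the limit. Those who fail are patients allocated above 50 who lose too little, or patients who gain.
- **A reader might infer that anyone above 50 at surgery is dropped.** The modified intention-to-treat definition keeps every patient operated on as allocated, and nothing says that surgery is cancelled above 50.
- **A reader might infer that the arms lose patients unequally.** BMI is a measured number, the same limit applies to both arms, and no mechanism for a difference is documented. There is no data monitoring committee, but independent auditing takes place at least annually.

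All of this limits the size of the problem and stands. It can also be said that a condensed article leaves the handling of patients found ineligible to the full protocol. That is fair for the handling rule, but not for the timing: the article states both dates, and no further detail can make a day-of-surgery value available at screening.

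Urged against required is a separate wording conflict. It neither supports nor depends on the main point.

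**Conclusion.** The point holds in a limited form. The upper BMI criterion cannot be verified at randomisation, and a randomised patient who exceeds it and is never operated on leaves the main analysis on a post-randomisation measurement taken with the arm known. This follows directly from the stated timings and needs no assumption.

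The size is not known. The article gives neither the BMI distribution near 50 nor the time from allocation to surgery, and the number affected may be small or nil. The figures above rest on assumed shares, an SD borrowed from pre-operative data and, for the shift in the estimate, loss confined to one arm. They show a modest effect even then. Unequal loss between arms is a risk, not a finding. The case for acting is that an avoidable post-randomisation eligibility test in an open trial can be removed at little cost.

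**What to change.** 1. **Inclusion criteria.** Keep the sponsor's limit, but judge trial eligibility on the last BMI measured before randomisation.
2. **Informed consent and randomization.** Defer randomisation of any patient still above the limit until a later pre-operative measurement meets it.
3. **Analysis of endpoints.** State that day-of-surgery BMI is not a reason to remove a randomised patient from the primary analysis. To have effect, this must also override the no-surgery exemption for a patient whose operation does not take place for that reason.
4. **Reporting.** Give, by arm, the number of randomised patients not operated on, with reasons.
5. **Wording.** Reconcile urged (Treatment) with required (Discussion).

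Whether and when to operate on a given patient stays a clinical decision for the sponsor.

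**Cost.** A short amendment to three sections. No new visit is needed, because physical examination is already scheduled at screening and at t = -1. Randomisation of a few patients near the limit would be delayed, and an occasional patient may regain weight above it after allocation. Under item 3, 12-month HbA1c should be sought for any patient kept in without surgery; otherwise the plan's last-value rule would carry a pre-operative value forward. The article describes recruitment as ongoing, with completion estimated for 2024. Items 1 and 2 can protect only patients not yet randomised; items 3 and 4 can cover everyone.

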### Exclusion criteria

Patients will be excluded on the following basis:Known genetic basis for insulin resistance or glucose intoleranceType 1 diabetes mellitusPrior bariatric surgeryAuto-immune gastritisGastro-esophageal reflux disease (confirmed by endoscopy or the use of a proton-pump inhibitor indicated by complaints of gastro-esophageal reflux)Known presence of a large hiatal hernia requiring concomitant surgical repairCoagulation disorders or a hemoglobinopathyUncontrolled hypertension (RR > 150/95 mmHg)Renal insufficiency (creatinine > 150 μmol/L)Pregnancy or breastfeedingAlcohol or drug dependencyParticipation in any other therapeutic study that may influence primary or secondary endpointsPatients who are considered incapable to fully understand the study and implications of participation in the study (e.g., as a consequence of a language barrier, psychiatric disease or mental disabilities) as judged by the coordinating researcher or the surgeon

